## Abstract

**Background:**

Quality of cardiopulmonary resuscitation (CPR) is associated with survival, but recommended guidelines are often not met, and less than half the children with an in-hospital arrest will survive to discharge. A single-center before-and-after study demonstrated that outcomes may be improved with a novel training program in which all pediatric intensive care unit staff are encouraged to participate in frequent CPR refresher training and regular, structured resuscitation debriefings focused on patient-centric physiology.

**Methods/design:**

This ongoing trial will assess whether a program of structured debriefings and point-of-care bedside practice that emphasizes physiologic resuscitation targets improves the rate of survival to hospital discharge with favorable neurologic outcome in children receiving CPR in the intensive care unit. This study is designed as a hybrid stepped-wedge trial in which two of ten participating hospitals are randomly assigned to enroll in the intervention group and two are assigned to enroll in the control group for the duration of the trial. The remaining six hospitals enroll initially in the control group but will transition to enrolling in the intervention group at randomly assigned staggered times during the enrollment period.

**Discussion:**

To our knowledge, this is the first implementation of a hybrid stepped-wedge design. It was chosen over a traditional stepped-wedge design because the resulting improvement in statistical power reduces the required enrollment by 9 months (14%). However, this design comes with additional challenges, including logistics of implementing an intervention prior to the start of enrollment. Nevertheless, if results from the single-center pilot are confirmed in this trial, it will have a profound effect on CPR training and quality improvement initiatives.

**Trial registration:**

ClinicalTrials.gov, NCT02837497. Registered on July 19, 2016.

**Electronic supplementary material:**

The online version of this article (10.1186/s13063-018-2590-y) contains supplementary material, which is available to authorized users.

## Background

Cardiac arrest occurs in 2–6% of patients admitted to a pediatric intensive care unit (ICU) [1]. Less than half survive to discharge [2–4]. Quality of cardiopulmonary resuscitation (CPR) is associated with survival [5–9], but recommended guidelines are often not met [5, 10]. Although standard courses are the mainstay of ongoing life support training, the evidence that these courses improve outcomes is modest [11–13]. Other approaches to improve CPR quality include real-time CPR feedback devices and structured postresuscitation debriefings. Real-time CPR feedback devices report quantitative CPR quality data (e.g., compression rate, depth, and release velocity) and have been moderately effective at improving psychomotor aspects of basic life support (e.g., chest compressions) [14, 15], but data demonstrating improved long-term outcomes are limited [16]. Comprehensive reviews (debriefings) of resuscitation efforts for the physicians involved in the resuscitation have improved CPR quality but have not been found to increase the rate of survival to hospital discharge [17]. Their lack of effectiveness may be due to traditional debriefing programs targeting only those providers who actually participated in the event under review [17]. However, a novel approach that incorporated patient-centric physiology into the review and included the entire care environment (i.e., both providers who were and those who were not at the resuscitation under review) has been associated with a higher rate of survival with favorable neurologic outcome [18, 19].

The generalizability of the benefits resulting from patient-centric physiologic debriefings with all potential providers of the care environment is unclear because this intervention has been evaluated only in a small, single-center before-and-after study [19]. The 42-month pediatric ICU study included an 18-month control period, a 6-month transition period, and an 18-month intervention period. The study enrolled 52 subjects with an index (first) CPR event in the control period and 42 subjects in the intervention period. The overall rate of survival with favorable neurologic outcome increased from 29% in the control period to 50% in the intervention period. Adjusting for potentially prognostic variables (age, sex, and first documented rhythm), subjects in the intervention period were more likely to survive to hospital discharge with favorable neurologic outcome (adjusted OR 2.75, 95% CI 1.01–7.5; *p* = 0.047) [19]. Despite limitations, the results suggest that this intervention may offer a powerful new approach for improving outcomes of in-hospital pediatric CPR. However, a multicenter randomized controlled trial is needed to assess the generalizability of these findings.

## Methods/design

The present study protocol was written in accordance with Standard Protocol Items: Recommendations for Interventional Trials (SPIRIT). A SPIRIT checklist is provided in Additional file 1.

### Objective

The primary aim of this ongoing multicenter trial, Improving Outcomes from Pediatric Cardiac Arrest – the ICU-Resuscitation Project (ICU-RESUS), is to assess whether structured debriefings for the ICU care environment combined with point-of-care bedside practice will improve the rate of survival with favorable neurologic outcome in children receiving CPR in the ICU.

### Design

Three types of designs were considered for this cluster randomized trial: a parallel design, a traditional stepped-wedge (TSW) design [20], and a hybrid stepped-wedge (HSW) design (Fig. 1). In a parallel design, each hospital is randomly assigned to either an intervention or control group for the duration of the trial. In a TSW design, each hospital begins enrolling in the control group and transitions to enrolling in the intervention group at a randomly assigned time. The design ultimately selected for this trial is an HSW design, which is a hybrid between the parallel and stepped-wedge designs. As in a parallel design, two randomly selected hospitals are permanently assigned to enroll in the control group, and two others are permanently assigned to enroll in the intervention group. The remaining six hospitals, as in a stepped-wedge design, initially enroll in the control group but are randomly assigned a time to transition to enrolling in the intervention group. However, it is important to note that the influence of the intervention on hospital staff and thereby on patient outcomes is not fully effective on the day that the intervention is initiated. Therefore, each of these six hospitals has a brief transition period during which outcome data will not be included in the analysis. To our knowledge, ICU-RESUS is the first implementation of an HSW design, one with several advantages in the context of the trial.

**Fig. 1 Fig1:**
[figure not shown]
Comparison of cluster-randomized trial designs. This figure illustrates the concept of a hybrid stepped-wedge (HSW) design compared with a parallel group or traditional stepped-wedge (TSW) design. **a** Parallel design. **b** TSW design. **c** HSW design

An HSW design, like a TSW design, offers a logistically feasible way to roll out a seemingly desirable intervention for participating hospitals at staggered intervals while also allowing a robust comparison between treatment and control periods. In particular, the design enables valid comparisons in the midst of underlying temporal trends in the outcome. In contrast, a simple before-and-after design, as in the single-center pilot study, cannot adequately account for temporal trends, and any observed “intervention effect” cannot be disentangled from other influencing factors that may have changed over time. In addition to the advantages of a TSW design, an HSW design has been reported, in many instances, to have increased power compared with a TSW design or a parallel group design [21].

### Intervention

The intervention is a two-part ongoing training program for ICU staff. The program includes structured debriefings for the entire care environment [19] (i.e., any care provider from several disciplines: physicians, nurses, respiratory therapists, extracorporeal support specialists) and point-of-care practice with a manikin [22].

A 1-h CPR debriefing is held approximately monthly (at least nine times per year) by the unit, and all ICU staff are encouraged to attend. Providers are “invited” to the sessions through emails and departmental flyers. Ideally, a recent resuscitation from within the unit is selected, but a de-identified case from another unit or hospital may be used if needed. The purpose of these debriefings is to carefully review aspects of care that went well and aspects that could be improved [18]. The case introduction includes relevant patient history and details of the patient characteristics and medical management preceding CPR. The debriefing then includes event details such as precode cardiac rhythm, interruptions in compressions, defibrillation attempts with pre- and postshock rhythm, ventilation, compression rate and depth, and release velocity (leaning). When available, case presentations emphasize patient-centric physiologic CPR targets using arterial catheter pressure tracings and end-tidal CO_2_ waveforms. Cases may also include important aspects of pediatric postarrest care such as recognition of seizures [23–25], prevention of fevers [26], and avoidance of hypotension [27]. These sessions are protected under quality improvement guidelines at the individual institutions.

Point-of-care bedside practice allows ICU staff to practice chest compression delivery on a manikin that is set up on a cart so that it can easily be brought to the clinicians throughout the unit. Manikins are equipped to monitor and provide real-time feedback on the quality of delivery (e.g., rate, depth, and release velocity). Both infant and child manikins are available for staff to practice on a model that is relevant to their patients for the shift. Point-of-care practice is frequent (≥ 48 per unit each month), but brief (< 2 minutes) in duration. This component of training was in place during both the control and intervention periods of the single-center pilot study of team debriefings and has been described previously [22, 28–30].

### Participants

ICU-RESUS is supported by the National Heart, Lung, and Blood Institute (NHLBI) and conducted by the *Eunice Kennedy Shriver* National Institute of Child Health and Human Development-funded Collaborative Pediatric Critical Care Research Network (CPCCRN). Hospitals were eligible for participation if they had not implemented either of the elements of the ICU-RESUS intervention and were committed to not implementing the intervention until scheduled by the trial randomization. The ten participating hospitals are geographically diverse tertiary care pediatric hospitals with patients from a mixture of urban, suburban, and rural areas of the United States [31]. These hospitals include 18 distinct units from which subjects will be enrolled.

All eligible subjects at participating institutions are enrolled under a waiver of consent. The central institutional review board at the University of Utah granted a waiver of consent based on the following factors:ICU-RESUS poses no more than minimal risk, because CPR training already exists in the ICUs and resuscitation quality should be at least as good with the ICU-RESUS intervention.The study involves no therapeutic intervention at the patient level, because the intervention is targeted to the care environment and does not deviate from accepted clinical practice.Obtaining informed consent would threaten the scientific validity of the study, which depends on capturing all eligible events during the enrollment period.

Subjects are considered for eligibility if they (1) are ≥ 37 weeks gestational age and ≤ 18 years of age and (2) receive CPR in the ICU. Subjects are excluded if they, prior to the arrest, (1) had a preexisting terminal illness and were not expected to survive the hospitalization (e.g., patients transferred to the ICU for end-of-life care); (2) had a lack of commitment to aggressive ICU therapies; (3) were brain dead; or (4) had an out-of-hospital cardiac arrest associated with the current hospitalization. CPR events lasting < 1 minute will be excluded from analysis if a site investigator determines CPR to have been unnecessary.

We anticipate enrolling 1540 index CPR events from 18 clinical units at 10 participating hospitals during a 4.5-year enrollment period. A schedule of enrollment, interventions, and assessment is provided in Fig. 2.

**Fig. 2 Fig2:**
[figure not shown]
Schedule of enrollment, interventions, and assessments. This figure illustrates the schedule of trial events, including enrollment, interventions, and assessments. Point-of-care practice occurs ≥ 48 times per month in each transitioned or transitioning intensive care unit (ICU). Debriefing occurs at least nine times per year at each transitioned or transitioning ICU. *CPR* Cardiopulmonary resuscitation, *PCPC* Pediatric Cerebral Performance Category scale, *PRISM* Pediatric Risk of Mortality score, a measure of illness severity based on assessments from 2 to 6 h prior to the CPR event

### Randomization

The role of randomization in an HSW trial is to determine which clusters will permanently enroll in the control group, which will enroll permanently in the intervention group, and the order in which the others will transition from control to intervention (Fig. 1c). Although the analysis will control for each individual unit, randomization occurs at the hospital level as opposed to the unit level to prevent the possibility of contamination. If units within a hospital were allowed to transition at different times, the intervention in one unit might inadvertently influence outcomes in the other, nontransitioned unit. One way that contamination could happen is through staff members from a transitioned unit temporarily working a shift in the nontransitioned unit. Therefore, when multiple units from a hospital are participating in the trial, all units are assigned the same transition date, reducing the possibility of contamination.

All possible permutations of the hospitals were considered for the order in which hospitals would transition from control to intervention. However, some permutations lead to a transition schedule in which the smallest hospitals transition early and the largest hospitals transition late, causing more subjects to be enrolled in the control group than in the intervention group. The imbalance for each permutation was estimated on the basis of hospital-specific enrollment expectations, and permutations with excessive imbalance were excluded. The permutation selected for implementation was then chosen at random from permutations with adequate balance with respect to expected enrollment between intervention and control groups.

The timing of the intervention for each hospital was established by the data coordinating center prior to enrollment. At a participating hospital randomly selected to transition from control to intervention, investigators and trial staff are informed of their selection 3 months prior to the assigned transition date. This time frame was selected to provide hospitals with sufficient notice to prepare for implementation while not divulging assignment so far in advance as to potentially affect a hospital’s resolve to stay the course. The scheduled hospital is allowed a 4-week window to begin the transition by holding an inaugural debriefing. The exact dates marking the beginning and end of the transition period, a period during which newly enrolled subjects are excluded from analysis, is determined by the date on which the first and fourth debriefings are held. Debriefings are held monthly, making the transition period approximately 3 months.

### Outcome assessment

As in the single center pilot study, the primary outcome is survival to hospital discharge with favorable neurologic outcome. Neurologic outcome is measured with the Pediatric Cerebral Performance Category scale (PCPC [32]) (Table 1) as per standard Utstein-style reporting guidelines [33]. Survivors are considered to have a favorable neurologic outcome if they have no worse than moderate disability at hospital discharge (PCPC score of 1, 2, or 3) or if their PCPC is no worse than at baseline. Baseline PCPC is retrospectively assessed in enrolled patients and is typically based on their status prior to the event leading to the current hospitalization. However, baseline PCPC is evaluated no more than 30 days prior to CPR for subjects who have been in the hospital for more than 90 days. Subjects who are born during the same hospitalization in which the CPR occurred will have their baseline PCPC assessed based on their status prior to the decompensation associated with the CPR event. PCPC assessment is performed by unblinded research coordinators on the basis of detailed objective criteria [32].

**Table 1 Tab1:** Pediatric Cerebral Performance Category scale

Score	Category	Description
1	Normal	At age-appropriate level; school-age child attend regular school
2	Mild disability	Conscious, alert, able to interact at age-appropriate level; regular school but grades perhaps not age-appropriate, possibility of mild neurologic deficit
3	Moderate disability	Conscious, age-appropriate independent activities of daily living; special education classroom and/or learning deficit present
4	Severe disability	Conscious, dependent on others for daily support because of impaired brain function
5	Coma or vegetative state	Any degree of coma, unaware, even if awake in appearance, without interaction with the environment; no evidence of cortex function; possibility for some reflexive response, spontaneous eye-opening, sleep-wake cycles
6	Brain death/death	Brain death, death

### Sample size calculation

In the single-center pilot, the intervention was associated with an increase in survival with favorable neurologic outcome from 29% to 50% (21 percentage points). We anticipate that we will see improvement to a rate similar to that achieved in the single-center pilot, but preliminary data from another study show that CPCCRN hospitals have a higher average baseline rate of survival with favorable neurologic outcome than the single-center pilot [34]. Therefore, our goal was to select a design and sample size that would provide approximately 80% power (at a significance level of α = 0.05) to detect a more conservative increase from 40% to 51% in survival with favorable neurologic outcome. An important factor for sample size calculation in cluster-randomized trials is the intracluster correlation (ICC), a measure of the similarity in outcomes among patients in the same cluster compared with outcomes among patients in different clusters [35]. The ICC was assumed to be 3% on the basis of pilot data from the multicenter Therapeutic Hypothermia after Pediatric Cardiac Arrest In-Hospital Trial [36].

The power and sample size estimates used for planning this trial were based on the method introduced by Hussey and Hughes [37], though generalized to allow for transition periods and implemented in PASS version 15 software [38]. This method uses a Wald Z-test to evaluate a null hypothesis of no effect against a two-sided alternative. We considered several trial design configurations, including parallel group, TSW, and HSW designs. We also investigated the impact of transition duration. With an ICC of 3%, an HSW design was found to be optimal (Table 2) [21, 39]. Long transition periods in HSW and especially in TSW designs increased the trial duration necessary to achieve > 80% power (Table 2). Therefore, an HSW design was selected with short (3-month) transitions.

**Table 2 Tab2:** Required duration of enrollment to achieve > 80% power

	Duration of enrollment (years)^a^
Trial design	
Parallel	NA^b^
Traditional stepped-wedge	
6-month transition	6
3-month transition	5.25
Hybrid stepped-wedge	
6-month transition	4.75
3-month transition	4.5

^a^Duration of enrollment is the approximate number of years required to achieve > 80% power to detect an increase from 40% to 51% in the rate of survival with favorable neurologic outcome

^b^In this context, a parallel design cannot achieve 80% power, regardless of the duration of enrollment

To estimate power for the HSW design, we assume that two hospitals, each with two units, are randomly assigned to begin with the intervention, and similarly that four units at two hospitals are assigned to remain as control hospitals for the duration of the study. Enrollment was assumed to be evenly distributed across the 18 units and also across the 18 time periods. A 3-month transition period was included for each of the ten transitioning units in the design-pattern matrix (Table 3). Units are the clusters used for sample size calculations and planned analyses. However, as noted above, randomization occurs at the hospital level to minimize the possibility of intervention contamination between units within a hospital. We found that analyzing 1256 index events (4 per unit per period) would provide 77% power to detect an 11-percentage-point increase in the rate of survival with favorable neurologic outcome from a baseline rate of 40%. Power increases to 84% when analyzing 1570 index events (5 per unit per period). On the basis of concavity of the power curve, analyzing 1391 subjects provides > 80% power. On the basis of historical CPR rates in participating units, we anticipate enrolling 1540 index events over the 4.5-year enrollment period. An estimated 48 index events will occur during the transition periods, allowing analysis of the remaining 1492 events and providing > 80% power.

**Table 3 Tab3:** Design-pattern matrix for sample size calculations in a 4.5-year hybrid stepped-wedge design with 3-month transitions

Unit	Time period (18 × 3 months)																	
	T1	T2	T3	T4	T5	T6	T7	T8	T9	T10	T11	T12	T13	T14	T15	T16	T17	T18
1	0	0	0	0	0	0	0	0	0	0	0	0	0	0	0	0	0	0
2	0	0	0	0	0	0	0	0	0	0	0	0	0	0	0	0	0	0
3	0	0	0	0	0	0	0	0	0	0	0	0	0	0	0	0	0	0
4	0	0	0	0	0	0	0	0	0	0	0	0	0	0	0	0	0	0
5	0	0	0	0	0	0	0	0	0	0	0	0	0	0	0	.	1	1
6	0	0	0	0	0	0	0	0	0	0	0	0	0	0	0	.	1	1
7	0	0	0	0	0	0	0	0	0	0	0	0	.	1	1	1	1	1
8	0	0	0	0	0	0	0	0	0	0	0	0	.	1	1	1	1	1
9	0	0	0	0	0	0	0	0	0	.	1	1	1	1	1	1	1	1
10	0	0	0	0	0	0	0	0	0	.	1	1	1	1	1	1	1	1
11	0	0	0	0	0	0	.	1	1	1	1	1	1	1	1	1	1	1
12	0	0	0	0	0	0	.	1	1	1	1	1	1	1	1	1	1	1
13	0	0	0	.	1	1	1	1	1	1	1	1	1	1	1	1	1	1
14	0	0	0	.	1	1	1	1	1	1	1	1	1	1	1	1	1	1
15	1	1	1	1	1	1	1	1	1	1	1	1	1	1	1	1	1	1
16	1	1	1	1	1	1	1	1	1	1	1	1	1	1	1	1	1	1
17	1	1	1	1	1	1	1	1	1	1	1	1	1	1	1	1	1	1
18	1	1	1	1	1	1	1	1	1	1	1	1	1	1	1	1	1	1

Each cell represents the intervention status of a unit in a given 3-month period. Zero indicates that the unit has not started the intervention; 1 indicates that the unit has completed the transition; and a dot indicates that the unit is in midtransition

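### The stated power above 80% assumes that units of the same hospital are independent; at the same 3% ICC it lies between about 75% and 82%, depending on how much of that ICC is shared within hospitals

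*Protocol article*

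**What the plan says.** The protocol article is open about its choice of cluster. The Sample size calculation section states: "Units are the clusters used for sample size calculations and planned analyses". It adds that "randomization occurs at the hospital level to minimize the possibility of intervention contamination between units within a hospital". The Randomization section confirms that hospitals are what is permuted ("All possible permutations of the hospitals were considered for the order in which hospitals would transition from control to intervention") and that all units of a hospital receive the same transition date.

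On the correlation, the same section says: "The ICC was assumed to be 3% on the basis of pilot data". The pilot data come from a multicentre trial. Neither the level of this ICC (unit or hospital) nor any correlation between units of one hospital is given.

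The target is about 80% power at α = 0.05 "to detect a more conservative increase from 40% to 51% in survival with favorable neurologic outcome". On the test: "This method uses a Wald Z-test to evaluate a null hypothesis of no effect against a two-sided alternative". The stated results are 77% at 1256 analysed events, 84% at 1570, and more than 80% at 1391. For the planned total it says: "An estimated 48 index events will occur during the transition periods, allowing analysis of the remaining 1492 events", again with more than 80% power.

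The Statistical analysis section includes unit as a random effect and mentions no hospital term.

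**The concern.** If two units of one hospital have correlated outcomes and always share the same intervention status, they carry less information about the intervention than two independently randomised units. A calculation that treats them as independent then overstates power. An analysis with a unit effect only also understates the standard error.

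The protocol explains why hospitals are randomised (contamination between units) but gives no reason to expect no shared hospital effect. Its own example, staff of one unit working a shift in another, suggests that units of a hospital have something in common.

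Two things are at stake. A null result would be read against a power claim that may be a few points too high, and the primary test may reject too often under the null.

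**Working it through.** **Inputs (Sample size calculation section).** Rates 40% and 51%, so the difference is 0.11. ICC 0.03. Two-sided Z at 0.05. Table 3 has 18 × 18 = 324 cells, less 10 transition cells, which leaves 314. Events per cell are m = N/314: 4 at 1256, 4.43 at 1391, 4.75 at 1492 and 5 at 1570.

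**Model.** Hussey-Hughes weighted least squares with categorical periods. Total variance is 0.40 × 0.60 = 0.24. The between-cluster part is τ² = 0.03 × 0.24 = 0.0072 and the within-cluster part is σ² = 0.97 × 0.24 = 0.2328. Let f be the share of τ² that lies at hospital level. The covariance of two cell means is

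f·τ² if same hospital + (1 − f)·τ² if same unit + σ²/m if same cell.

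SE is the square root of the treatment entry of (D′V⁻¹D)⁻¹, where D holds the period and treatment columns and V is the covariance matrix. Power ≈ Φ(0.11/SE − 1.96). Each identical pair of rows in Table 3 is taken as one hospital.

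**Step 1: reproduce the plan (f = 0).** Power is 77.3% at 1256, 80.3% at 1391 and 83.6% at 1570, which matches the stated 77%, more than 80%, and 84%. At 1492, SE = 0.0381, 0.11/SE = 2.88 and power is 82.2%. The stated figures therefore correspond to no shared hospital effect.

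**Step 2: keep everything and vary f (an assumption; the protocol gives no split).**

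| Share of ICC at hospital level | Power, 1391 events | Power, 1492 events |
|---|---|---|
| 0% | 80.3% | 82.2% |
| 25% | 77.9% | 79.9% |
| 50% | 76.0% | 78.1% |
| 75% | 74.4% | 76.6% |
| 100% | 73.1% | 75.4% |

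Worked example for 100% at 1492: SE = 0.0416, 0.11/SE = 2.65, Φ(2.65 − 1.96) = 75%.

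**Step 3: layout.** Table 3 has five transitioning pairs, so nine two-unit blocks, whereas the trial has ten hospitals, six of them transitioning. Ten-hospital layouts gave about 76–79% (half shared) and 73–77% (all shared), so the loss does not come from the Table 3 pairing.

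**Step 4: type I error of a unit-only model at 1492 events, variance components known.** The model reports a variance of 0.00145 for the effect. The true variance is 0.00165 (half shared) or 0.00185 (all shared).
- Half: 1.96 × √(0.00145/0.00165) = 1.84, two-sided 6.6%.
- All: 1.96 × √(0.00145/0.00185) = 1.74, two-sided 8.2%.

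Simulation with estimated components gave about 6% (none shared), 7% (half) and 12% (all). It used normal cell means and linear time, not the planned logistic model with covariates.

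**The case against.** The strongest reply is that nothing is miscalculated. Every stated figure reproduces, the choice of units as clusters is disclosed, and the goal was only about 80% power. This stands in part: the issue is an unsupported assumption, not an arithmetic slip, and a fall to 75–78% is modest against that goal. But disclosing an assumption does not justify it, and the claim of more than 80% carries no qualification.

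Second, the hospital share is not in the documents. That is correct. A reader might infer that true power simply is 75–78%. The documents do not support this, because it requires half or more of the ICC to be shared. An ICC taken from a multicentre trial may well be a centre-level figure, but this cannot be confirmed. Only the range across shares is defensible.

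Third, the planned covariates may raise power, and the calculation takes no credit for them. As an illustration only, a 10% cut in residual variance (assumed, linear scale) would give 81.3% with half shared and 78.8% with all shared. The protocol says only that the covariates may help, so this softens the concern but does not replace a stated calculation.

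Finally, a reader might go further and apply a t reference with 8 degrees of freedom for the ten hospitals, giving about 64–67% with half to all of the ICC shared. That overstates the loss: the t test had a simulated size of only about 3–4%, so it is conservative. Tests calibrated to about 5% gave roughly 70–77%. The choice of a small-sample method may also sit in an analysis plan that is not shown.

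**Conclusion.** The concern holds as a conditional one. The claim of more than 80% power rests on treating units of one hospital as independent although hospitals are randomised. At 1492 events it survives only if less than about a quarter of the 3% ICC is shared at hospital level. The 1391 figure has almost no margin, at 80.3% with nothing shared.

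The likely size is moderate: 2 to 5 points below 80% if half to all of the ICC is shared. In effect terms, the difference detectable with 80% power, (1.96 + 0.84) × SE, is 2.80 × 0.0402 = 11.3 points (half shared) or 2.80 × 0.0416 = 11.6 points (all shared), against the planned 11. The unit-only primary model matters at least as much, since it lets the type I error exceed 5% under the same conditions.

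These results assume a total ICC of 3%, equal enrolment per cell, the Table 3 pattern and a linear-scale approximation. They do not show that the trial is seriously underpowered.

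**What to change.** 1. State whether the 3% ICC is at unit or hospital level.
2. Recompute power with units nested in hospitals, the actual layout (ten hospitals, six transitioning) and the hospital-specific enrolment expectations already used to restrict the randomisation.
3. Replace the single claim of more than 80%, and the 1391 figure, with power across the hospital share: about 75–82% at 1492 events under the Table 3 pattern.
4. Add a hospital random effect to the primary model, with units nested in it, so that the analysis matches the randomisation.
5. If power for a small-sample test is also reported, use one calibrated to 5% (roughly 70–77% here) and label it as dependent on assumptions.

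The cost is a recalculation, a few restated sentences and one more variance component in the model. The stated power becomes slightly less favourable. No extra enrolment is needed.
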